## Abstract

**Background:**

Chronic nonspecific low back pain (CNLBP) is among the most prevalent health problems. Lumbar spine and hips kinematics and coordination can be affected in CNLBP. The effects of exercises on the kinematics and coordination of lumbar spine and hips during sit-to-stand (STS) and its reverse have not been evaluated.

**Objective:**

The aim of this study is to investigate the effect of core stabilization exercise on the kinematics and joint coordination of the lumbar spine and hip during STS and its reverse in CNLBP patients.

**Methods:**

COSCIOUS is a parallel randomized double-blind controlled trial. A total of 30 CNLBP patients and 15 asymptomatic participants will be included. The kinematics and joint coordination of the lumbar spine and hips will be evaluated during STS and its reverse using a motion capture system. The participants will be asked to sit in their usual posture on a stool. Reflective markers will be placed over the T12, S2, anterior and posterior superior iliac spines, greater trochanters, and lateral femoral epicondyles of both legs. The participants will be instructed to stand up at natural speed, remain in the erect posture for 3 seconds, and then sit down. Kinematic variables of the lumbar spine and hip will be computed. Afterward, the CNLBP participants will be allocated at random to receive one of 2 interventions: core stabilization or general exercise. Treatment sessions will be held 3 times per week for 16 sessions. After intervention, CNLBP participants will be assessed again.

**Results:**

Funding for the study was provided in 2016 by Iran University of Medical Sciences. The study is expected to last approximately 12 months, depending on recruitment. Findings on the study’s primary outcomes are expected to be finalized by December 2017. The results of the study will be published in a peer-reviewed journal.

**Conclusions:**

This investigation will evaluate the effects of core stabilization exercise on the kinematics and joint coordination of the lumbar spine and hip during STS and its reverse in patients with CNLBP. In addition, the effects of CNLBP on STS and its reverse will be investigated in COSCIOUS.

**Trial Registration:**

Iranian Registry of Clinical Trials IRCT2016080812953N2; http://en.search.irct.ir/view/32003?format=xml (Archived by WebCite at http://www.webcitation.org/6qjTWd4Az)

## Introduction

Low back pain (LBP) is defined as pain between the 12th rib and inferior buttock crease with or without leg pain [1,2]. According to the Global Burden of Disease Study, LBP is a major cause of years lived with disability in all continents and economies [3], and it is one of the main causes of absenteeism in industrialized societies [4]. Chronic low back pain (CLBP) is generally defined by symptoms that persist for a period of longer than 3 months (12 weeks) [5,6]. However, there is no precise definition of CLBP in the literature [7]. In some studies, CLBP is described as pain that lasts longer than 7 to 12 weeks, whereas the others define this condition as pain that lasts longer than expected with conventional treatment [7]. Due to no consensus regarding the definition of CLBP, there is a wide variation in the prevalence estimates reported in the literature [8]. However, Parthan et al [8] mentioned that the prevalence of CLBP ranges from 4% to 14%.

LBP is frequently associated with changes in the mobility of the lumbosacral region and hip [9-12]. Normal spinal mobility is required for optimal activities of daily living performance, and it has been shown that impairment of spinal mobility can result in various forms of functional disabilities [13], which may have serious adverse effects on quality of life [12]. Patients with LBP have been shown to have some limitations in both spinal and hip motion that compromise their function. In addition, Marras and Wongsam [14] indicated that the coordination between the lumbosacral region and hip is decreased during standing forward bending in patients with LBP. However, their simple descriptions of range of motion (ROM) and a simple forward bending task that do not adequately explore coordination between movements of the lumbosacral region and hips limit the generalizability of their findings to the functional tasks [12-14].

Sit-to-stand (STS) movement and its reverse, which are considered fundamental prerequisites for daily activities, are repeated many times throughout the day [12]. It has been shown that this movement could be performed about 60 times per day in workers [15]. In addition, STS movement is a skill [16], and the ability to perform this movement is a key factor in the maintenance of functional independence [17]. The manner in which STS movement is described depends somewhat on the aim of the study. For example, in the Roebroeck et al [18] study, STS movement is defined as traveling the body’s center of mass (COM) upward from a sitting position to a standing position without losing balance [18]. Vander Linden et al [19] defined STS movement as a transitional movement to the upright posture and requiring movement of the COM from a stable position to a less stable position over extended lower extremities. Schenkman et al [20] defined STS movement in more detail and divided it into 4 phases. Phase I (or *flexion-momentum phase*) begins with initiation of the movement and terminates just before the buttocks are lifted from the seat of the chair (lift-off). During this phase, the trunk and pelvis rotate anteriorly and the femurs, tibias, and feet remain stationary [20]. Phase II (or *momentum-transfer phase*) starts when the buttocks are lifted and terminates when maximal ankle dorsiflexion is achieved. During this phase, the COM moves anteriorly and upward [20]. Phase III (or *extension phase*) is begun just after maximum ankle dorsiflexion and completes when the hips first cease to extend, including leg and trunk extension. This phase is terminated when the hip extension angular velocity reaches 0° per second [20]. Phase IV (or *stabilization phase*) initiates after hip extension angular velocity reaches 0° per second and terminates when all motion associated with stabilization is completed [20]. Furthermore, Shum et al [12] divided STS movement into 2 phases: flexion and extension. The flexion phase begins with initiation of the movement and terminates when maximum flexion of the lumbar spine and hips is achieved (first 2 phases of Schenkman et al [20] classification). The extension phase starts just after phase I and continues until the end of the movement (last 2 phases of Schenkman et al [20] classification).

In 2005, Shum et al [12] evaluated the kinematics and joint coordination of the lumbar spine and hip during STS and its reverse in patients with acute LBP using an electromagnetic tracking device (3SPACE Fastrak system). The results of their study indicated that the mobility of the spine and hips and contribution of the lumbar spine relative to the hip were decreased in individuals with acute LBP. Furthermore, the lumbar spine–hip joint coordination was significantly altered in acute LBP subjects [12]. However, this study was conducted on acute LBP patients, and the data obtained from these participants is not representative of the population with chronic nonspecific low back pain (CNLBP). In addition, Shum et al [12] evaluated only the kinematics and joint coordination, and the effect of intervention on the kinematics has not been assessed. They recommended that further research is needed to evaluated the effect of intervention.

A core stabilization exercise program is described as facilitation of the deep musculature of the spine (primarily the transversus abdominis or multifidus) at low-level sustained isometric contraction, integrated into exercise and finally, progressing into functional tasks. The core stabilization exercise uses motor learning principles to facilitate coordination of the deep musculature of the spine [21-23]. It is usually delivered in 1:1 supervised treatment sessions and sometimes comprises palpation or ultrasound imaging or the use of pressure biofeedback units to provide feedback about the activation of trunk musculature [23].

To the best of authors’ knowledge, this study for the first time aims to investigate the effect of core stabilization exercise on the kinematics and joint coordination of the lumbar spine and hip during STS and its reverse in patients with CNLBP (COSCIOUS). The main objectives of COSCIOUS are as follows:

To determine the kinematics and joint coordination of the lumbar spine and hip during STS and its reverse in patients with CNLBP and asymptomatic participantsTo determine the effect of core stabilization exercise on the kinematics and joint coordination of the lumbar spine and hip during STS and its reverse in patients with CNLBP

Macedo et al [24] mentioned that core stabilization exercise can optimize the control and coordination of the spine. However, there is not sufficient evidence to clearly support this claim that core stabilization exercise has superior effects on joint coordination compared to general exercise. Therefore, the secondary objective of this study is to determine the effect of general exercise on the kinematics and joint coordination during STS and its reverse in CNLBP. We hypothesized that there are significant differences between the results in patients with CNLBP and healthy participants during STS and stand-to-sit movements. In other word, ROM, maximum displacement, and angular velocity of the lumbar spine and hips would be decreased in CNLBP. Furthermore, we hypothesized that exercise therapy would have a significant positive impact on the kinematics and coordination in CNLBP patients. It is hoped that COSCIOUS would help clinicians and physical therapists evaluate the functional disabilities of patients with CNLBP, who are a big population in LBP patients. In addition, we hope that if this study exercise therapy protocol has a more positive effect on the kinematics and joint coordination, it can be used as a guideline for the treatment of functional disabilities (especially this important functional movement) in populations with CNLBP.

## Methods

### Study Design and Ethics

COSCIOUS is a parallel, randomized, double-blind controlled trial with 2 experimental groups and one asymptomatic (control) group. It is a part of the PhD thesis of the first author ([name]) and will be conducted in the biomechanics laboratory located at the School of Rehabilitation Sciences, Iran University of Medical Sciences (Tehran, Iran). The level of evidence of this investigation is level Ib. Ethical review and approval for COSCIOUS was obtained from the Research Ethics Committee at Iran University of Medical Sciences (Ethical Approval Number: IR.IUMS.REC 1395.9211342207) on July 27, 2016. The trial is registered at the Iranian Registry of Clinical Trials [IRCT2016080812953N2].

### Participants

A total of 30 patients with CNLBP and 15 demographically matched asymptomatic (healthy) participants will be recruited for COSCIOUS. The sample size of CNLBP patients is determined based on previous studies that have evaluated the effect of lumbar extension exercise on the kinematics of the lumbar spine and hips during a common daily activity [25,26]. Steele et al [26] calculated the sample size for their study and reported that a minimum of 7 participants would be required in each group to achieve 80% power at an alpha level of *P* ≤.05 [26]. Therefore, 45 participants will be divided into 3 groups: 2 experimental groups (15 patients with CNLBP in each group) and one healthy control group (15 asymptomatic participants). Considering some attrition, the sample size was increased to 15 participants in each group. The CNLBP patients will be identified and recruited by posters, emails, and word of mouth from the university and the surrounding locality. Direct referral also will be provided from 2 orthopedic surgeons and 2 neurologists in Tehran. Inclusion criteria of COSCIOUS are as follows:

CNLBP (LBP persisting for more than 3 months in the absence of an underlying pathology)Aged between 18 and 40 yearsPain between 3 and 6 at rest on a 0- to 10-point pain visual analog scale (VAS), where 0 represents no pain and 10 is the worse pain imaginableAbility to perform STS movement and its reverse without an aidNo contraindication for exerciseNo obvious deformity of the spine, pelvis, and lower extremitiesNo autoimmune diseases (eg, rheumatoid arthritis) [12]No pregnancy

In this study, we will try to balance some of most important prognostic indicators of LBP such as educational status, smoking, working status, age, gender, and pain intensity in 2 treatment groups [27,28]. This strategy will help minimize the effects of confounding variables. Participants who do not complete the treatment sessions (absence for 3 consecutive or a total of 5 sessions) will be excluded from the study. Before participation in this study, procedure of this investigation will be explained both verbally and in writing, and written informed consent will be obtained from all participants. In addition, the participants will be assured that their personal information will be kept confidential (confidentiality principle). Participants will be identified only by initials and participant number on the research notes. All study results and completed questionnaires will be anonymized. All trial documents will be stored securely and not accessible to people outside of the research team. Participants will be withdrawn from this investigation if there are any concerns regarding informed consent.

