### Procedure

#### Initial Assessment

After the recruitment process is complete and agreement to participate is obtained, participants will be brought into the biomechanics laboratory of the School of Rehabilitation Sciences, Iran University of Medical Sciences (Tehran, Iran). To ensure the activity is as natural as possible, few constraints will be placed on the procedure of STS movement and its reverse. Participants will not be allowed to use their hands to push up, and the feet should stay on the floor [12]. In order to standardize head posture and prevent the negative impact of the thoracic and cervical spines on lumbar spine kinematics, a visual target (white A4 paper with a black circle drawn upon it) will be adjusted to eye level in front of participants [31]. Data collection will begin with the capture of a reference standing posture. Then, participants will be asked to sit in their usual posture on an adjustable stool with neither armrest nor backrest. The stool provides support from the ischial tuberosities to the middle of the thighs. Foot placement will not be restricted and participants will be requested to relax their arms, hanging them next to their thighs. The stool height is 110% of knee-floor length, which is defined as the distance between the floor and the apex of the fibular head [12]. Participants will be instructed to stand up at their self-selected normal speed following a loud voice command (“Start”) and remain a comfortable and erect posture for 3 seconds. They will then be asked to sit down on the chair at their own comfortable speed and maintain this position for 3 seconds. Each subject will repeat the movements 3 times, and the mean data will be used for statistical analysis. Asymptomatic participants will serve as a control group in the first assessment in order to detect differences in kinematic parameters during STS and its reverse between the CNLBP patients and asymptomatic participants. Hence, they will not participate in the intervention phase and the second assessment (Figure 1).

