### Statistical Analysis

Statistical analyses will be performed on a personal laptop using SPSS for Windows release version 21.0 (IBM Corp) and STATA version 13 (StataCorp LLC). The comparability of asymptomatic participants and CNLBP patients on disability level, pain intensity, and kinematic variables at baseline will be analyzed using the independent *t* tests for parametric and Wilcoxon test for nonparametric distribution. In addition, a mixed-model 2-way analysis of variance (ANOVA) for each dependent variable (disability level, pain intensity, maximum joints ROM, joint angular velocities, lumbar/hip motion ratios, and maximum and minimum relative phase differences), with the 2 factors being group (core stabilization/general exercise) and time (preintervention/postintervention). After intervention, comparison between core stabilization group, general exercise group, and asymptomatic participants will be made using the ANOVA test (*Scheffe* post hoc tests). In addition, an intention-to-treat analysis will be conducted if any protocol deviation is observed at the end of the study due to attrition or loss to follow-up. Perceived pain and functional disability will be compared with consensus standards for minimal clinically important change (MCIC) [48]. Ostelo et al [48] considered the MCIC for VAS as 15 mm and for RMDQ as 5 points for patients with LBP. Furthermore, effects sizes will be measured using the Cohen *d* [49]. Statistical significance level is set at *P* ≤.05.

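### The asymptomatic group is demographically matched, but the baseline kinematic comparison with patients is an unadjusted t or Wilcoxon test, which is valid but uses the matching factors inefficiently

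*Protocol article*

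**What the plan says.** The Participants section sets the sample. Besides the 30 patients, "15 demographically matched asymptomatic (healthy) participants will be recruited". It names neither the matching factors nor whether matching is person by person or at group level.

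The Initial Assessment section gives the purpose of this group. It serves as a control at the first assessment "in order to detect differences in kinematic parameters during STS and its reverse between the CNLBP patients and asymptomatic participants". The Introduction lists this comparison as the first of two main objectives and expects lower range of motion, displacement and angular velocity in patients.

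The Statistical Analysis section fixes the method. Before treatment, the two groups are compared on pain, disability and kinematics, and these data "will be analyzed using the independent *t* tests for parametric and Wilcoxon test for nonparametric distribution". After the intervention, a "comparison between core stabilization group, general exercise group, and asymptomatic participants will be made using the ANOVA test", with Scheffé post hoc tests. Neither analysis includes a covariate, a stratum or a matched-set term.

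The only other balancing in the article concerns prognostic factors "such as educational status, smoking, working status, age, gender, and pain intensity in 2 treatment groups", that is, the two randomized arms and not patients against asymptomatic participants.

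**The concern.** Controls are selected on demographic factors, and the analysis then treats the two groups as if those factors were unknown. This comparison is not randomized, so demographic differences can be handled only by the selection of controls or by the analysis.

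Two different things can follow, depending on how the matching works out:

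- **Close matching.** The group means of the matching factors are nearly equal, so those factors add little to the true variability of the mean difference. The t test still counts their full contribution in its standard error. If the factors predict the outcome, the standard error is too large and the test is conservative.
- **Loose matching.** The standard error is then roughly right, but any remaining demographic difference between the groups goes straight into the estimate.

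At stake are the precision and interpretation of the first main objective. The randomized comparison is not involved.

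**Working it through.** **The plan's own figure.** The only sample-size figure is 7 per group for 80% power at α = 0.05, borrowed from an earlier study and raised to 15 for attrition. Its effect size and SD are not given, so it cannot be reproduced. It also does not concern this comparison, and nothing below rests on it.

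**Inputs**

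- From the article: 30 patients, 15 asymptomatic participants, α = 0.05.
- Assumed: two-sided testing; a true difference d = 0.8 SD; three covariates; R² from 0 to 0.3. None of these is in the document.

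**Step 1. Unadjusted test, no matching.**
Standard error in SD units = √(1/30 + 1/15) = √0.1 = 0.316. Noncentrality = 0.8/0.316 = 2.53. Degrees of freedom = 45 − 2 = 43. Power (noncentral t) = 69.6%.

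**Step 2. Adjusted test.**
The residual SD falls by the factor √(1 − R²), so the noncentrality is 0.8/√(1 − R²)/0.316, with 43 − 3 = 40 degrees of freedom. The CI-width ratio is √(1 − R²) × t(0.975; 40)/t(0.975; 43) = √(1 − R²) × 2.021/2.017.

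| R² | Noncentrality | Adjusted power | CI width, adjusted/unadjusted |
|---|---|---|---|
| 0 | 2.53 | 69.5% | 1.002 |
| 0.1 | 2.67 | 74.0% | 0.951 |
| 0.2 | 2.83 | 78.8% | 0.896 |
| 0.3 | 3.02 | 83.9% | 0.838 |

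**Step 3. What the unadjusted test achieves under close matching.**
The 69.6% in step 1 ignores matching. Close matching already removes some noise from the mean difference, so the t test gains a little power even though its standard error is overstated. Simulating matched sets of one control and two patients with one matching covariate gives:

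| R² | t test, true type I error | t test, power | Adjusted power | Gain |
|---|---|---|---|---|
| 0 | about 5% | about 70% | about 70% | 0 points |
| 0.1 | about 4% | about 71% | about 74% | 3 points |
| 0.2 | about 3% | about 72% | about 79% | 7 points |
| 0.3 | about 2% | about 73% | about 84% | 11 points |

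The adjusted analysis keeps its type I error at about 5% throughout.

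**Step 4. Loose matching.**
If a matching factor still differs by δ SD between the groups, the unadjusted difference is biased by √R² × δ. For δ = 0.3 (assumed):

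- R² = 0.1: 0.316 × 0.3 = 0.09 SD
- R² = 0.2: 0.447 × 0.3 = 0.13 SD
- R² = 0.3: 0.548 × 0.3 = 0.16 SD

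**The case against.** The strongest reply is that the plan contains no error. An independent t test after matching is valid and errs on the safe side, so preferring a covariate model is a matter of efficiency. This stands. A reader might infer that the planned test risks false positives because it ignores the matching. The calculation shows the opposite under close matching: a true type I error of about 4% to 2% instead of 5%.

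Second, a reader might infer that imprecision and residual imbalance both apply in full. They are alternatives: closer matching leaves less imbalance to correct, and looser matching leaves less overstatement of the standard error. The article does not say which case applies. A reader might also set the adjusted powers against 69.6% and report gains of about 4, 9 and 14 points. That baseline assumes no matching; under close matching the gains are 3, 7 and 11.

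Third, the size rests on assumed values, and R² may be small. Patients are limited to ages 18 to 40 without obvious deformity, and stool height is scaled to each person's knee-floor length, which removes part of any body-size effect. This also stands. At R² = 0 adjustment gains nothing.

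Fourth, the matching factors may be listed in a fuller document. Their absence from the article is not held against the plan here. The point is that the article itself names the test, and that test has no place for them.

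**Conclusion.** The point holds as an optional improvement to the analysis of the first main objective. The article matches the asymptomatic group on demographics and then fixes tests that take no account of those factors, although a better method is available at almost no cost.

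For 30 versus 15 with d = 0.8, two-sided α = 0.05 and close matching, adjustment is worth about 0, 3, 7 and 11 points of power at R² = 0, 0.1, 0.2 and 0.3. The 95% CI is 0.2% wider at R² = 0 and about 5%, 10% and 16% narrower at the other values. If matching is loose, the reason to adjust is instead the imbalance left in the estimate. R², d, δ and the number of covariates are assumptions, and the type of matching is not stated.

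The documents do not support calling the planned t test invalid, and nothing here bears on core stabilization versus general exercise.

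**What to change.** For the kinematic variables, and the coordination variables where patients and asymptomatic participants are compared, replace the baseline t or Wilcoxon tests by a linear model with group plus the demographic factors actually used for matching. Age and gender are examples only; the article does not name the factors. Report the adjusted mean difference with a 95% CI. Pain and disability need no such model, because patients are selected on pain.

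If matching is individual, add a matched-set term, preferably as a random effect. Were each control matched to two patients, fixed effects for 15 sets would use 14 of the 43 degrees of freedom and leave 29.

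The change is one analysis sentence and needs no new participants or visits, since matching requires that the factors be recorded. It costs two or three of 43 degrees of freedom. With 45 people the covariate list should stay that short; a long list of categorical factors would use up the gain. The post-intervention three-group ANOVA, which also uses the asymptomatic group without covariates, could be aligned at the same time.

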Following the assessment, CNLBP participants will be randomly divided into 2 groups (core stabilization exercise and general exercise) for treatment. First, all CNLBP participants will perform warm-up exercises that consist of 8 stretching exercises (hamstrings, quadriceps, latissimus dorsi, and iliotibial band of both sides; 1 set of 5 repetitions with a 10-second hold per repetition) and stationary bicycling for a period of 10 minutes [37,38]. Based on the previous recommendations, a staged approach will be followed for both groups [38] (see Multimedia Appendix 1). This approach includes 8 exercise levels with progressively increasing difficulty [38]. In the first session, the exercises will be explained and demonstrated to CNLBP participants. We will try to use the Template for Intervention Description and Replication checklist [39] as a guideline to improve the completeness of reporting of our intervention procedure.

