The same frequency (*3 times per week*; Saturday, Monday, Wednesday) and duration (6 weeks; 16 sessions) will be provided for both groups [37]. All treatment sessions will be held in the morning (8 AM to 12 PM). In each session, participants will be instructed to perform their exercises as many times as they can with rest periods in the same session. However, the holding time and number of contractions will be progressively increased up to 10 contraction repetitions × 10 second duration each [38]. Finally, exercise sets will be increased from 3 to 5 sets. The first session will last for 30 to 45 minutes, and the time of treatment session will be gradually increased in a dose-dependent manner. Based on Koumantakis et al [38] study, CNLBP participants in the core stabilization exercise group will be asked to activate their muscles at about 30% of their maximum activation level during the performance of stabilization exercises, and CNLBP participants in the general exercise group will be asked to activate their muscles at about 60% to 70% during the performance of general exercises. However, in the core stabilization exercise group, heavier load functional tasks, with exercises similar to those conducted by CNLBP participants in the general exercise group, will be progressively introduced in the last 6 sessions of the program [37]. All exercises will be performed under supervision of an experienced physical therapist. Moreover, to control confounding variables and create a standard and homogeneous condition for all CNLBP participants, they will be instructed not to perform exercises at home between the treatment sessions. Treating physical therapist will explain the positive effects of exercise on health in each session to improve adherence of CNLBP participants to intervention protocol. Any deviations from the exercise protocol, such as the receipt of any additional interventions or therapy for LBP, will be recorded and the decision will be made on whether the participant should be excluded from the study.

After 16 treatment sessions, all CNLBP participants will be evaluated again in the same manner as the initial assessment. Pain intensity and functional disability will be measured using the VAS and the Persian translated version of the RMDQ. Figure 1 illustrates a Consolidated Standards of Reporting Trials (CONSORT) diagram of this study.

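### Randomised patients can be excluded for missed sessions or protocol deviations, which conflicts with an intention-to-treat analysis that is only a conditional addition

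*Protocol article*

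**What the plan says.** All references are to the protocol article.

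- **Order of events (Initial Assessment).** "Following the assessment, CNLBP participants will be randomly divided into 2 groups (core stabilization exercise and general exercise) for treatment". Randomisation follows the baseline measurement and precedes the first session.
- **Attendance rule (Participants).** "Participants who do not complete the treatment sessions (absence for 3 consecutive or a total of 5 sessions) will be excluded from the study".
- **Deviations (General Exercise).** Departures from the exercise protocol, including other therapy for back pain, "will be recorded and the decision will be made on whether the participant should be excluded from the study". No criterion is given and no decision-maker is named.
- **Second assessment (General Exercise).** "After 16 treatment sessions, all CNLBP participants will be evaluated again in the same manner as the initial assessment".
- **Analysis (Statistical Analysis).** Each dependent variable gets a mixed two-way ANOVA with arm and time (before and after intervention) as factors. As a further step, "an intention-to-treat analysis will be conducted if any protocol deviation is observed at the end of the study due to attrition or loss to follow-up".

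**The concern.** Every absence and every deviation happens after randomisation, so both exclusion rules act on patients who already belong to an arm. Intention-to-treat means analysing all of them in that arm. The article promises such an analysis, but elsewhere it removes from the study some of the patients it would have to include, and it does not secure a post-treatment measurement for them.

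This matters because attendance and seeking other care may depend on pain, on response and on the assigned programme. The article gives some reason to expect this. General Exercise asks for about 30% of maximum activation in the core arm and about 60% to 70% in the general arm. Management of Adverse Events foresees patients reporting more pain between appointments. Participants and Limitations both expect some loss. What is at stake is the only randomised comparison in the trial, with 15 patients per arm, where each exclusion removes 1/15 = 6.7% of an arm.

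**Working it through.** **1. The rules side by side**

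| Question | Exclusion rules (Participants, General Exercise) | Statistical Analysis |
|---|---|---|
| Who stays in? | Not those with three absences in a row or five in all; possibly not those with deviations or extra therapy | All randomised patients, if the intention-to-treat analysis is triggered |
| When does it apply? | Whenever the event occurs | Only for deviations arising from attrition or loss; exclusion by the investigators is not clearly covered |
| Is an outcome secured? | Not stated for excluded patients | The pre/post ANOVA needs a post value for each patient |
| Which result leads? | – | Not stated; intention-to-treat is an addition |

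The attendance rule reaches patients with substantial exposure. Five missed sessions of 16 leaves 11/16 = 69% attended. Three in a row, with no other absence, leaves 13/16 = 81%.

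**2. The plan's own allowance for loss**

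Participants raises a minimum of 7 per group to 15 for attrition but states no rate. The step corresponds to 1 − 7/15 = 53% loss, which cannot be read as a forecast. The 7 itself cannot be reproduced, because no effect size or SD is given. The exclusion counts below are therefore assumptions.

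**3. Bias, simple form**

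Let a fraction p of an arm be excluded, with outcomes δ SD worse than those retained. The full-arm mean is (1 − p)m + p(m − δ) = m − pδ, where m is the mean of those retained. The retained mean is thus too favourable by pδ, and the contrast between arms is biased by (p₁ − p₂)δ. For the group-by-time test, the outcome is the pre-to-post change.

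- 3/15 v 1/15, δ = 1: 0.200 − 0.067 = 0.13 SD
- 3/15 v 1/15, δ = 0.5: 0.07 SD
- 5/15 v 0/15, δ = 1: 0.33 SD
- 3/15 v 3/15, δ = 1: 0 between arms, but each arm's own mean is too favourable by 0.20 SD

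**4. Bias, by simulation**

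Setting: 15 per arm, no true difference, the poorest attenders removed, two-sample t test at two-sided 0.05, 40,000 runs per row. The correlation ρ between attendance and outcome is assumed.

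| Excluded | Bias in SD, ρ = 0.3 / 0.5 / 0.7 | Type I error |
|---|---|---|
| 3 v 1 | 0.063 / 0.103 / 0.146 | 5.4% / 6.4% / 7.9% |
| 3 v 0 | 0.099 / 0.162 / 0.227 | 5.7% / 7.3% / 9.5% |
| 5 v 0 | 0.155 / 0.258 / 0.360 | 6.7% / 9.3% / 14.9% |
| 3 v 3 | about 0 (each arm shifted by 0.099 / 0.163 / 0.230) | 4.9% / 5.8% / 6.7% |

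The last row shows that selection can raise the type I error a little even without bias between arms, so not all of the excess in the other rows comes from bias.

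**5. Precision**

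Detectable standardised difference, two-sample t test, two-sided 0.05, 80% power:

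- 15 v 15: 1.06
- 12 v 14 (the 3 v 1 case): 1.15
- 12 v 12: 1.20

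With two time points, the group-by-time test is equivalent to a t test on change scores, so these values are in SDs of change. In SDs of the raw outcome they would depend on the pre-post correlation, which is not stated.

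**The case against.** The strongest reply is that the article does commit to intention-to-treat when patients are lost. If nobody is lost or excluded, completers and all randomised patients are the same set and the condition costs nothing. A reader might infer that the comparison is simply a completer analysis; the text does not support that, because attrition triggers some intention-to-treat analysis. What remains is that the trigger does not clearly reach exclusions made under the attendance or deviation rules, and that precedence is unset.

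A reader might also infer that excluded patients get no second assessment. No sentence says so. The article speaks of all patients being evaluated again, and the reference to 16 sessions may mark the end of the programme. It cannot literally require full attendance, since the attendance rule tolerates four absences that are not too closely grouped (12/16 = 75% attended). The flow diagram (Figure 1) could not be read for this check and might say more. Being excluded from the study nevertheless suggests no follow-up, and nothing in the text secures it.

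The deviation rule may remove nobody, since it only calls for a decision. That stands, but a decision without a stated criterion remains open to influence by response.

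How missing values enter an intention-to-treat analysis is commonly left to an analysis plan and is not counted here. Such a plan could specify imputation, but it could not recover measurements that were never taken.

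Finally, the illustrated bias of 0.13 SD is about one eighth of the detectable 1.06 (0.13/1.06 = 0.12) and rests on assumed inputs. That is fair: the size is uncertain and may be small.

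**Conclusion.** The concern holds as a conflict between stated rules. Randomised patients can be excluded for events after randomisation, while intention-to-treat is an additional analysis with a trigger that may not cover them. As written, the main group-by-time ANOVA would rest mainly on patients who attended enough and were remeasured.

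A reader might go further and conclude that the randomised comparison is necessarily biased. The documents do not show this. Bias between arms needs exclusions that are related to outcome and that differ between arms. If they are related to outcome but equal across arms, the contrast is unbiased on average, but the pre-to-post change within each arm is still distorted, and the article lists the effect of core stabilisation exercise among its main objectives.

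Under the assumed scenarios, the bias between arms runs from about 0.06 SD (3 v 1 excluded, weak link to outcome) to 0.36 SD (5 v 0, strong link), with 0.13 SD for the simple 3 v 1 case. The actual size cannot be fixed from the article. The conflict should be resolved in the protocol before follow-up, because missed assessments cannot be recovered later.

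**What to change.** - **Participants.** Replace exclusion for missed sessions with wording such as: *will be recorded as non-adherent but remain in the study*.
- **General Exercise, deviations.** Record deviations and co-interventions without excluding the patient from follow-up or from the main analysis.
- **General Exercise, second assessment.** Invite every randomised patient to the second assessment at one fixed time after randomisation, whatever the attendance.
- **Statistical Analysis.** Make the analysis of all randomised patients by assigned arm the main analysis, without a condition. Use the rule of three absences in a row or five in all only to define a supportive per-protocol set.

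These changes concern follow-up and analysis; they do not alter the exercise programmes. The cost is changed wording, second visits for non-attenders, and possible dilution of the estimated effect by non-adherence. Some non-attenders may still decline the visit, so some missing data may remain.
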